## Abstract

**Introduction:**

Degenerative lumbar spinal stenosis is a common cause of low back or leg pain and disability in the elderly population. Patients with spinal stenosis who fail to respond to conservative treatment often require surgical interventions. Minimally invasive transforaminal lumbar interbody fusion (TLIF) with microscopic tubular technique (MT-TLIF) is a well-established procedure for lumbar spinal stenosis. Recently, a novel MIS technique, unilateral biportal endoscopic TLIF (UBE-TLIF), has been frequently performed to treat spinal stenosis. However, the efficacy and safety of using UBE-TLIF in this population have not been well examined.

**Methods and analysis:**

A total of 96 patients with lumbar spinal stenosis will be randomly assigned to the UBE-TLIF group or the MT-TLIF group at a 1:1 ratio to receive UBE-TLIF or MT-TLIF treatment respectively. The primary outcome is the Oswestry Disability Index (ODI) score at 1 year after receiving the surgery. Secondary outcomes include the ODI scores at additional time points, Visual Analogue Scale score, 36-Item Short Form Survey questionnaire, EuroQol 5 Dimensions questionnaire, radiological measurements (disc height, lumbar lordosis angles and vertebral fusion rate) and general condition during hospitalisation.

**Ethics and dissemination:**

This protocol is approved by the Medical Ethics Committee of the Third Affiliated Hospital of Sun Yat-sen University. All participants of the study will be well informed and written informed consent will be requested. Findings from this trial will be published in peer-reviewed publications, specifically in orthopedic and spinal journals. The completion of this study will not only examine the use of UBE-TLIF in lumbar spinal stenosis but also provide helpful clinical references.

**Trial registration number:**

ChiCTR2300069333.

STRENGTHS AND LIMITATIONS OF THIS STUDYThis is a prospective, randomised controlled, non-inferiority clinical study to compare the surgical procedure of unilateral biportal endoscopic transforaminal lumbar interbody fusion (TLIF) with microscopic tubular technique TLIF for the treatment of degenerative lumbar spinal stenosis in terms of the clinical safety and efficacy.All surgeries are performed by surgeons who have 10-year operation experience and are familiar with the two surgical procedures.The data are collected from a single institution with a relatively small sample size.The surgeons cannot be blinded for the study because the intervention is surgery and the protocols for two surgeries are different.

## Introduction

 Degenerative lumbar spinal stenosis (DLSS) can cause a series of symptoms, such as low back and leg pain as well as intermittent claudication. Patients who fail to respond to conservative treatment often require surgery interventions.^1^ It is generally agreed that for patients who have severe spinal stenosis and (or) spondylolisthesis, sufficient neural decompression and lumbar interbody fusion have been demonstrated to be an effective approach to improve clinical outcomes.^2 3^ However, traditional open surgery is associated with a series of drawbacks such as abundant blood loss, significant damage to soft tissue and long hospital stay.^4 5^

Anand *et al* first reported the microscope-assisted transforaminal lumbar interbody fusion (TLIF) technique which has the advantages of smaller incision, less soft tissue damage, decreased blood loss and enhanced postoperative recovery compared with the open surgery.^6^,^8^ With the development of surgical technique and instrument, the biportal endoscopic spinal fusion was first implemented in 2012 by Osman *et al* and Dong Hwa Heo *et al* first used minimally invasive TLIF with biportal endoscopic in 2017.^9 10^ Previous studies show that unilateral biportal endoscopic TLIF (UBE-TLIF) has less blood loss, reduced postoperative pain and faster postoperative recovery compared with conventional methods.^11 12^ Moreover, due to the high-definition field of view, the separation of the working and the observation channel in UBE-TLIF is relatively more convenient.^13^ However, it has the disadvantages such as relatively deep learning curve, limited indications and long operation time, which may increase perioperative complications.^14^ Therefore, its efficacy is uncertain, and there is still no high-level evidence to support whether UBE-TLIF is non-inferior to microscopic tubular technique (MT-TLIF) in terms of clinical outcomes up to now.

Here, a prospective, randomised controlled, non-inferiority clinical study was designed to compare the surgical procedure of UBE-TLIF with MT-TLIF for the treatment of DLSS in terms of the clinical safety and efficacy in detail.

### Research aim

The purpose of this study is to test whether UBE-TLIF is non-inferior to MT-TLIF in treating patients with DLSS in terms of efficacy and safety.

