### Outcome measurements

#### Primary outcome

The main outcome of the study is the ODI score at 1-year postoperation, which is a 10-item questionnaire specific to low back pain patients, including pain intensity, personal care (washing, dressing etc), lifting, walking, sitting, standing, sleeping, sex life (if applicable), social life and travelling. Each of the 10 items is scored from 0 to 5. Total scores are calculated by dividing the actual by the maximum score of 50 and converting it to a percentage. The score of 100% is recognised as the highest score, signifying the greatest dysfunction severity.^19 20^

The minimal clinically important difference (MCID) is a threshold value that patients and clinicians perceive as clinically meaningful. The clinically acceptable MCID in reported ODI scores is 8–12. However, to date, there is no consensus on calculating the optimal MCID for the ODI scores in groups.^21^,^23^ Consequently, following discussion, we adopted 8 as the MCID within clinically acceptable range. By comparing the ODI score 1 year after surgery, we can determine whether UBE-TLIF is not inferior to MT-TLIF within the non-inferiority margin of 8.

Considering that the condition of most enrolled subjects will be stabilised at 1-year postoperation, the assessment time frame of 1-year ODI is between 12 and 15 months after the operation. In case subjects do not return to the hospital for follow-up on time during this period, a telephone follow-up will be conducted to complete the ODI questionnaire.

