### Sample size

The MCID for ODI scores reported in similar studies is 8–12.^22 23^ After discussing among experienced professors from the spine surgery department, 8 in ODI score is chosen as the margin of non-inferiority (ðN) in this study. Based on the Consolidated Standards of Reporting Trials 2010 statement,^28^ it is assumed that the expected response is the same in both groups, the estimated true difference between the two surgeries is 0, and the ðN is 8. The SD is estimated to be 13 based on previous studies.^29^ The test level is one sided (α=0.025), and the test power (1−β) is 0.8. Considering that 10% of population may loss to follow-up, a total of 96 subjects are required in this clinical study.

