### AE and serious AE

Surgery-related AEs from both arms will be reported and documented throughout the study period.

Intraoperative complications include dural tear, nerve root injury, pedicle screw misplacement, endplate fracture, cardiopulmonary complications, allergic reactions and other unpredictable complications. Postoperative complications include cerebrospinal fluid leakage, neurological deficit or deterioration, excessive postoperative drainage volume (>400 mL/day), postoperative infection, surgery-related thrombotic events, pedicle screw breakage, cage subsidence or migration, cardiopulmonary complications, haematoma within the spinal canal and other unpredictable complications.^30^,^32^

During the intervention and follow-up periods of this trial, any AE will be identified promptly and managed properly.

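### The stated aim extends the non-inferiority test to safety, but the only margin and the only sample-size basis are for 1-year ODI

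*Protocol article*

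**What the plan says.** The Research aim section gives the purpose in one sentence: to "test whether UBE-TLIF is non-inferior to MT-TLIF in treating patients with DLSS in terms of efficacy and safety". As worded, safety is an object of the non-inferiority test alongside efficacy.

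The sections that put this into operation concern ODI only:

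- **Primary outcome:** "The main outcome of the study is the ODI score at 1-year postoperation". By comparing that score, the section says, "we can determine whether UBE-TLIF is not inferior to MT-TLIF within the non-inferiority margin of 8".
- **Sample size:** "8 in ODI score is chosen as the margin of non-inferiority". The other inputs are "the estimated true difference between the two surgeries is 0", "The SD is estimated to be 13 based on previous studies" and "The test level is one sided (α=0.025), and the test power (1−β) is 0.8". With 10% loss to follow-up, the total is 96, randomised 1:1.

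On safety, Statistical analysis defines a safety set of operated patients in whom adverse events are recorded. AE and serious AE lists intraoperative and postoperative complications and says: "Surgery-related AEs from both arms will be reported and documented throughout the study period". Neither section names a comparative safety endpoint, an expected rate, a margin or a decision rule. Statistical analysis assigns Pearson chi-square to categorical variables, with two-sided p<0.05. Fusion rate is the only categorical variable it names.

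**The concern.** A non-inferiority test needs an endpoint, a margin and enough information to exclude a difference as large as that margin. The article supplies these for 1-year ODI and for nothing else, so the aim claims more than the design provides.

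This is not a detail that a statistical analysis plan can be presumed to supply. The margin and sample-size basis are stated in this article, and they stop at ODI. A later document could add a safety margin, but it could not turn 96 into a number chosen for safety.

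Safety is also a question the article raises itself: the Introduction lists drawbacks of UBE-TLIF that could lead to more perioperative complications. If the final report took its conclusion from the aim as worded, it could describe the newer operation as non-inferior in safety when the data cannot show it.

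**Working it through.** **1. Where the 96 comes from.** Inputs from Sample size: margin 8, SD 13, true difference 0, one-sided alpha 0.025, power 0.80, 10% loss.

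- Normal approximation: n per arm = 2 × [13 × (1.960 + 0.842) / 8]² = 41.45, rounded up to 42. Then 42 / 0.9 = 46.7, rounded up to 47 per arm, or 94 in total.
- Noncentral t: 42 per arm gives power 0.796 and 43 gives 0.805, so 43 are needed. Then 43 / 0.9 = 47.8, rounded up to 48 per arm, or 96 in total, an exact match.

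The ODI inputs account for the whole sample size. It has no safety component.

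**2. What 48 per arm can say about complications.** The article gives no complication rate, so the rates below are assumptions. With the same true rate p in both arms, the approximate 95% half-width for the risk difference is 1.96 × √[2p(1−p)/48]:

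| Assumed rate p | Half-width (percentage points) |
|---|---|
| 5% | 8.7 |
| 10% | 12.0 |
| 15% | 14.3 |

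With 43 per arm the values are 9.2, 12.7 and 15.1.

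**3. Power of a two-sided 5% chi-square test to detect a doubling, if such a test were used.** For 10% versus 20%:

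- pooled SE = √(2 × 0.15 × 0.85 / 48) = 0.0729
- unpooled SE = √[(0.10 × 0.90 + 0.20 × 0.80) / 48] = 0.0722
- power = Φ[(0.10 − 1.96 × 0.0729) / 0.0722] = Φ(−0.59) ≈ 0.28

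The same formula at other base rates gives:

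| Assumed rates | Power |
|---|---|
| 5% vs 10% | 15% |
| 10% vs 20% | 28% |
| 15% vs 30% | 42% |
| 20% vs 40% | 57% |

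**4. Power of a formal safety non-inferiority test at 48 per arm.** The article states no margin, so three are shown for illustration only. With one-sided alpha 0.025 and equal true rates, power = Φ[margin / SE − 1.96], where SE = √[2p(1−p)/48]:

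| Illustrative margin | Power, assumed rates 5% to 20% (highest at 5%) | Total N for 80% power with 10% loss |
|---|---|---|
| 5 points | 20% down to 9% | 666 to 2234 |
| 10 points | 61% down to 23% | 168 to 560 |
| 15 points | 92% down to 45% | 76 to 250 |

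Of the combinations shown, only the lowest rate with the widest margin (5% with 15 points) reaches 80% power at 96 patients.

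**The case against.** The strongest reply is that the aim is loosely worded and states no second confirmatory hypothesis. The Primary outcome and Sample size sections already tie non-inferiority to ODI, and the Discussion closes by saying only that the trial will compare efficacy and safety. The article lists its small sample as a limitation and calls for larger multicentre studies to confirm efficacy and safety. The data safety monitoring committee reviews safety data throughout. How complications are tabulated, and how intervals are formed, is commonly left to the full protocol or analysis plan.

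Much of this stands. The absence of a tabulation or interval method is no finding. Two stronger readings should also be resisted:

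- **That safety will be judged by a chi-square p-value.** A reader might infer this from the general rule for categorical data. The article does not list adverse events among the variables so tested, and purely descriptive reporting is equally compatible with its text.
- **That a non-significant result will be read as equally safe.** This is a foreseeable misuse, but the article states no such plan.

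The figures are also limited. The rates are assumed, and the complication list is broad. At 5% only 48 × 0.05 = 2.4 events per arm are expected, so the normal approximation is rough there. An interval of ±12 points is still informative, because it can exclude large differences.

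The point survives because it needs neither inference. Description alone cannot establish safety non-inferiority, and neither can a non-significant difference test. Acknowledging a small sample and having committee oversight do not supply a margin. The aim still says that safety non-inferiority will be tested.

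**Conclusion.** The point holds as a mismatch between the stated aim and the design. Non-inferiority is defined and powered for 1-year ODI only, so a claim of non-inferior safety would have no support. This conclusion rests on the text and needs no assumed rate.

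The size of the gap does rest on assumptions, namely the complication rates and, for non-inferiority power, the illustrative margins. Under those used here, 48 per arm leaves an uncertainty of about 9 to 14 points either side for rates of 5% to 15%. A doubling would be missed in about 43% to 85% of trials for base rates of 20% down to 5% (100% minus the power in step 3).

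The ODI sample size is correct and the primary ODI comparison is untouched. The aim should be corrected because it governs what the trial may conclude about the newer operation.

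**What to change.** Reword the aim so that non-inferiority is tested for 1-year ODI only and safety is a descriptive comparison. Carry the same limit into the conclusions.

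For safety, report the number of patients with at least one complication in each arm, with the risk difference and its 95% confidence interval. Use an exact or score-based interval because counts may be small. Add one sentence saying that absence of a significant difference will not be taken as evidence of equal or non-inferior safety.

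The cost is a slightly narrower stated scope and a few changed sentences. No extra patients, visits or data are needed, and the ODI analysis and the total of 96 stay as they are.

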## Methods and analysis

### Patient and public involvement

There is no patient and/or public involvement in the overall design, conduct, reporting or dissemination of this study. The expected study duration is from February 2023 to March 2025.

### Study design and settings

This is a prospective, randomised, controlled, non-inferiority clinical study. A total of 96 eligible patients will be randomly assigned to the MT-TLIF arm or UBE-TLIF arm at a 1:1 ratio and receive treatments at the Third Affiliated Hospital of Sun Yat-sen University. A diagram of the trial design is shown in figure 1. The primary outcome is the Oswestry Disability Index (ODI) score at 1-year postoperation. The study has been registered and can be accessed online on the China Clinical Trial Registration Center website (https://www.chictr.org.cn/), with the registration date being 14 March 2023. Trial registration data of this study is in online supplemental table 1.

**Figure 1 F1:**
[figure not shown]
Study flow chart. EQ-5D, EuroQol 5 Dimensions; ODI, Oswestry Disability Index; SF-36, 36-Item Short Form Survey; UBE, unilateral biportal endoscopic; VAS, Visual Analogue Scale.

### Patient selection

A trained research nurse will introduce the trial to the subjects and have a discussion with them. Written consent will be obtained from subjects who are willing to participate in the trial. This study will include patients aged between 30 and 80 years with the lower extremity pain and/or neurogenic intermittent claudication and confirmed by MRI as single-level DLSS. X-ray confirmed degenerative or isthmic spondylolisthesis ≤grade II in Meyerding grade, or lumbar spine instability, or decrease in disc height (DH) accompanied by intervertebral foraminal stenosis. Moreover, these symptoms persist for at least 3 months before the surgery. The inclusion and exclusion criteria are presented in table 1.

**Table 1 T1:** Inclusion and exclusion criteria

Inclusion criteria	Exclusion criteria
Age 30–80 years old	Highly degenerative and isthmus bifida spondylolisthesis (Meyerding grade III and IV)
Lower extremity pain and/or neurogenic intermittent claudication, and confirmed by MRI as single-level degenerative lumbar spinal stenosis	Narrowing or slipping of more than one segment that requires decompression or fusion of more than two segments
Degenerative or isthmus fissure ≤Meyerding grade II, or lumbar vertebra instability (forward or posterior sagittal displacement ≥3 mm or ≥8%, or sagittal angle change ≥15°) or decrease in DH accompanied by intervertebral foraminal stenosis	Presence of any other neurological disease or vascular disease of the legs that may interfere with the study assessment
Symptoms lasting at least 3 months before surgery	Any segment fusion surgery of the lumbar vertebra
Sign the informed consent form, be able to understand the informed consent form and follow-up related questionnaires	Other spinal diseases (such as spinal infection, ankylosing spondylitis, other inflammatory spondylitis, spinal tumours, spinal trauma)
Agreed to comply with clinical protocols and willing to adhere to follow-up schedules and requirements	Failure to perform baseline and/or follow-up MRI or X-ray as required
	Cognitive and psychological disorders (such as Alzheimer’s disease, intellectual disability or substance abuse)
	Other diseases deemed inappropriate to participate in the study by the surgeons

DHdisc height

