#### Secondary outcome

The secondary outcomes of this study will assess ODI score at additional time points, VAS, SF-36, EQ-5D, radiological indicator (DH, LL angles and vertebral fusion rate) and hospitalisation information. The data collection schedule is presented in table 2. For those who cannot come for follow-ups, our research assistant will contact them by phone or email to complete the questionnaire.

**Table 2 T2:** The time schedule for collection of data for this trial

	Day≤−1	Day1	Day2–29	Day30±7 days	Day90±7 days	Day180±7 days	Day360±7 days
Inclusion and exclusion criteria	**√**						
Signing of informed consent form	**√**						
Demographic assessment	**√**						
Physical examination	**√**						
Operation time/Intraoperative blood loss		**√**					
Serum CK/CRP			**√**				
Length of stay			**√**				
ODI score	**√**			**√**	**√**	**√**	**√**
VAS score	**√**			**√**	**√**	**√**	**√**
SF-36-PF	**√**			**√**	**√**	**√**	**√**
SF-36-BP	**√**			**√**	**√**	**√**	**√**
QoL EQ-5D	**√**			**√**	**√**	**√**	**√**
Disc height	**√**				**√**	**√**	**√**
Lumbar lordosis angles	√				√	√	√
Vertebral fusion rate							**√**
Complications		**√**	**√**	**√**	**√**	**√**	**√**
Adverse events		**√**	**√**	**√**	**√**	**√**	**√**

√, This refers to the data collection at the scheduled time.

BPbody painCKcreatine phosphokinaseCRPC reactive proteinEQ-5DEuroQol 5 DimensionsODIOswestry Disability IndexPFphysical functioningQoLquality of lifeSF-3636-Item Short Form SurveyVASVisual Analogue Scale

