#### Radiological indicators

DH and LL angles are measured by X-rays. The reduction in DH correlates with the progression of intervertebral disc degeneration, characterised notably by intervertebral space stenosis. Thus, the magnitude of DH reduction serves as an indicator of the degenerative process’s severity. LL angles over 10° suggest progression risk in spondylolisthesis. The approach to measurement is meticulously detailed in the prior section. An experienced spine physician and radiologist with ten years of experience will simultaneously evaluate the intervertebral fusion of the subjects based on CT scans. The fusion criteria are shown in table 3.^27^

**Table 3 T3:** Bridwell intervertebral bone graft fusion evaluation system

Grade	Description
I	Fused with remodelling and trabeculae present
II	Graft intact, not fully remodelled and incorporated, but no lucency present
III	Graft intact, potential lucency present at top and bottom of graft
IV	Fusion absent with collapse or resorption of graft

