### Statistical analysis

In this study, three analysis sets will be required. For the safety analysis set, any adverse event (AE) will be recorded from patients who have undergone UBE-TLIF or MT-TLIF following randomisation. In the full analysis set, all participants who were randomised to the surgical intervention and for whom complete data sets were accessible after randomisation. In instances of missing data, we employed the last observation carried forward and baseline observation carried forward methods for imputation. For the per-protocol cohort, at least 90% of subjects should fulfil the following criteria: (1) receive either UBE-TLIF or MT-TLIF treatments; (2) with no violation of the protocol; (3) complete the full follow-up and (4) obtain all required data. Continuous variables, including VAS score, ODI score, operation time, intraoperative blood loss, serum CK and CRP level, DH, LL, SF-36, QoL EQ-5D as well as hospital stay, will be expressed as means±SDs, while categorical data, including vertebral fusion rate, will be shown as frequencies. The independent t-test and Pearson χ^2^ will be applied to analyse continuous and categorical variables, respectively. If indicated, statistical analysis between subgroups will be performed. All statistical analyses will be performed using Statistical Product and Service Solutions (V.26.0, IBM) by the principal biostatistician. A p<0.05 (two sided) will be considered statistically significant.

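### Table 1 makes missed follow-up imaging an exclusion criterion, which read literally turns an event after randomisation into ineligibility

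*Protocol article*

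**What the plan says.** - **Exclusion criterion.** Table 1 (Patient selection) excludes patients for "Failure to perform baseline and/or follow-up MRI or X-ray as required".
- **Related inclusion criterion.** The same table separately requires patients to be "willing to adhere to follow-up schedules and requirements".
- **When eligibility is checked.** In Table 2 (Secondary outcome) the row "Inclusion and exclusion criteria" is ticked once, at Day ≤−1.
- **When images are due.** Radiological indicators states that "DH and LL angles are measured by X-rays". Table 2 schedules both measures at baseline and at Days 90, 180 and 360.
- **Patients who do not return.** For the primary outcome, "a telephone follow-up will be conducted to complete the ODI questionnaire" when a patient does not attend on time. For secondary outcomes, "For those who cannot come for follow-ups, our research assistant will contact them by phone or email to complete the questionnaire".
- **Analysis sets.** Statistical analysis limits the full analysis set to randomised participants "for whom complete data sets were accessible after randomisation". It then says of missing data that "we employed the last observation carried forward and baseline observation carried forward methods for imputation". Completing follow-up and having all required data are conditions of the per-protocol set.

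**The concern.** Eligibility should rest on what is known before randomisation. The baseline half of the criterion does. The follow-up half describes something that can only happen months after surgery.

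If a site or analyst applies the line as written, a randomised and operated patient is reclassified as ineligible after the event. Attendance for imaging may depend on outcome: patients who are too disabled to travel, dissatisfied or fully recovered may all stay away. Removing them would mean comparing groups selected after treatment, for a primary endpoint (1-year ODI) that needs no image. In a non-inferiority trial, selective loss of this kind can produce a false conclusion of non-inferiority. It would also waste the telephone ODIs that the protocol sets out to collect.

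**Working it through.** **1. Timing.** Eligibility is assessed at Day ≤−1. Follow-up X-ray measures are due at Days 90, 180 and 360. No patient can have failed follow-up imaging when eligibility is assessed, so the follow-up half of the criterion can be met only after randomisation. No section limits it to inability or unwillingness known at screening.

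**2. Consistency with follow-up.** A patient who does not attend at 1 year can still give the ODI by telephone. If that patient also has no 1-year film, the protocol collects the primary outcome while Table 1, read literally, labels the patient excluded.

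**3. Consistency with the analysis sets.** The Statistical analysis section does not refer to Table 1 eligibility. It neither drops nor protects these patients. The complete-data condition of the full analysis set points towards dropping them, and the carry-forward imputation points towards keeping them.

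**4. The plan's own sample size.** Inputs from the Sample size section: margin 8, SD 13, true difference 0, one-sided α 0.025, power 0.80, loss 10%.
- Normal approximation: n = 2 × 13² × (1.960 + 0.842)² / 8² = 41.5, so 42 per arm. 42/0.9 = 46.7, so 47 per arm and 94 in total.
- t-test: 43 per arm gives power 0.805. 43/0.9 = 47.8, so 48 per arm and 96 in total.

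The stated 96 is reproduced.

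**5. How many patients could meet the criterion.** The document gives no miss rate. Assume that each of the three X-ray visits is missed with probability p. If misses are independent, the share missing at least one is 1 − (1 − p)³. If they cluster fully (the same patients miss every visit), the share is p.

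| p (assumed) | Fully clustered | Independent | Left per arm of 48, clustered | Left per arm of 48, independent |
|---|---|---|---|---|
| 3% | 3% | 8.7% | 46.6 | 43.8 |
| 5% | 5% | 14.3% | 45.6 | 41.2 |
| 10% | 10% | 27.1% | 43.2 | 35.0 |

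These figures take missed imaging as the only loss.

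**6. Power if all such patients were removed.** Noncentral t, noncentrality 8 / (13 × √(2/n)), one-sided 0.025:
- 43 per arm: 0.805
- 41 per arm: 0.786
- 35 per arm: 0.718
- 34 per arm: 0.705

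**7. Bias, for illustration.** Suppose removal shifts the observed ODI difference by b points in favour of UBE-TLIF when the true difference equals the margin of 8. With 10% removed (43.2 per arm), SE = 13 × √(2/43.2) = 2.80. The one-sided error is 1 − Φ(1.96 − b/SE): 0.025 for b = 0, and about 0.055, 0.107 and 0.187 for b = 1, 2 and 3. The shifts are assumed. The document supports neither their size nor their direction.

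**The case against.** The best defence is that Table 2 settles the timing. Because eligibility is checked only before surgery, the only workable meaning is that a patient unable or unwilling to have the required imaging is not enrolled. The plan to telephone or email non-attenders supports this, since it shows that they are meant to stay in the trial. This may well be what the authors intended. But the criterion names a failure to perform, which is an event and not an intention, and willingness already has its own inclusion criterion. No section states the narrower meaning.

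A reader might infer that the protocol removes these patients from the ODI analysis and discards their telephone questionnaires. The document does not support that. The analysis-set definitions do not mention Table 1 eligibility, and the section provides imputation for missing data. Removal is a risk left open, not a stated rule. Nor does every patient telephoned at 1 year lack X-rays, since the Day 90 and Day 180 films may exist.

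A reader might also take 9–27% as the expected loss. That range needs independent misses, whereas missed visits tend to cluster within patients. Under full clustering the same rates give 3–10%, which does not exceed the planned 10% loss.

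Finally, Table 2 has no MRI row, but little follows from this: the criterion offers MRI or X-ray as alternatives, and Table 2 lists measurements rather than imaging methods.

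**Conclusion.** The wording is defective and should be fixed. Taken literally, it makes ineligibility depend on an event after randomisation, and it sits badly with the remote collection of the ODI. The protocol does not say that affected patients leave the primary analysis. It does not rule this out either, and the complete-data condition of the full analysis set makes it more likely.

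The size of the effect cannot be derived from the document. The loss of power is small unless misses are both frequent and spread across patients: from 0.805 at 43 per arm to 0.71–0.72 at 34–35. Bias from selective removal is the more serious possibility, but its size and direction are unknown. The planned 96, the margin, the endpoint and the test are unaffected.

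**What to change.** - **Reword the Table 1 criterion** so that it rests on what is known before randomisation, for example: *baseline MRI or X-ray not done, or known inability or unwillingness to undergo the required baseline or follow-up imaging*. Deleting only the reference to follow-up would go too far. It would lose a valid screening ground, known inability to have follow-up imaging, which the willingness criterion does not cover.
- **Add one sentence to Statistical analysis**: missed follow-up imaging is missing radiological data, at most a deviation that affects the per-protocol set, and never removes a randomised patient from the primary ODI analysis. Bring the complete-data wording of the full analysis set into line with this.

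The cost is a short wording amendment, with no change to sample size, visits or assessments.
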